#### Secondary outcomes

##### Mental health outcomes

The mean change in WHO-5, GAD-7, and PAID-5 (for patients with diabetes) scores from baseline to follow-up at 6 and 12 months will be estimated using the same methods as for the primary outcome.

##### Somatic outcomes

Comparative analyses will estimate the mean change in total cholesterol levels (mmol/L), LDL levels (mmol/L) and (for patients with diabetes) HbA1c levels (mmol/mol) from baseline to 12 months using a generalised linear mixed model. The model will consider patient demographics, clustering, and time effects as described above.

##### Process outcomes

Descriptive analyses will estimate the extent of implementation (fidelity, dose, reach) and mechanisms of impact (mediators and unintended consequences). Process outcome data will be combined with effect outcome data to explore the associations between process and effect measures.

### Interim analyses {21b}

PST is a well-established treatment, which is considered safe and not expected to result in potentially serious adverse outcomes. Thus, no interim analyses are planned.

### Methods for additional analyses (e.g. subgroup analyses) {20b}

Exploratory subgroup analyses will be conducted to explore the potential differential effects of the intervention based on pre-specified characteristics of participating patients. These include sex, age, socioeconomic status, health literacy level, severity of mental health outcomes, and diagnosis (T2D or IHS). Furthermore, subgroup analysis will explore the impact of dosage received defined as a number of completed PST sessions, whether PST was provided by a GP or general practice staff, and the size of the general practice in which the intervention was delivered.

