##### The healthy mind intervention

All patients with T2D and/or CHD attending annual chronic care consultations in general practice are screened for poor mental well-being using the WHO-5 Well-Being Index (WHO-5) [19], described in detail in “Plans for assessment and collection of outcomes {18a}” section and in Table 1. In the intervention protocol, patients with a WHO-5 score < 50 points are offered PST provided by either the trained GP or practice staff. A booklet guiding patients through the five sequential steps of PST, facilitated by the healthcare professional, is provided. The booklet is designed by the research team based on the insights from the feasibility study [16]. Patients are offered up to seven 30-min PST sessions. In the control protocol, patients receive the usual care.

**Table 1 Tab1:** Participant timeline

Time point	Baseline	During or immediately after the intervention	6 months	12 months

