##### Process outcomes

The process outcome data are part of an explanatory sequential mixed methods process evaluation, guided by the UK Medical Research Council framework for process evaluations [30, 31]. Quantitative process outcome data are collected continuously throughout the study via the Healthy Mind website database. Information about fidelity and dose is collected through questionnaires completed by healthcare providers during the registration following each PST session. Reach data are extracted from trial-monitoring records, while data on mediators and unintended consequences come from questionnaires completed by both healthcare providers and patients after the patient’s final PST session.

Qualitative data will be collected through semi-structured interviews with purposefully selected patients (*n* = 10) after their final PST session. The interview guide will focus on reach, fidelity, mediators, and unintended consequences and will be informed by quantitative process measures from each individual patient. Qualitative interview data will be transcribed verbatim and analysed thematically. The process evaluation will be supplemented by ethnographic case studies exploring the role of context.

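### Completed PST sessions and actual provider are planned as subgroups, yet both arise after allocation and only under the intervention, so no subgroup effect is defined and within-intervention contrasts may be confounded

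*Protocol article*

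**What the plan says.** The section on additional analyses {20b} opens with a legitimate aim: "Exploratory subgroup analyses will be conducted to explore the potential differential effects of the intervention based on pre-specified characteristics of participating patients". The same paragraph then extends the term subgroup analysis to two variables of another kind. The first is dose: "subgroup analysis will explore the impact of dosage received defined as a number of completed PST sessions". The second is "whether PST was provided by a GP or general practice staff". Practice size is named in the same sentence.

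Elsewhere the article fixes how these variables come about:

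- **Dose.** In the intervention description, "Patients are offered up to seven 30-min PST sessions"; Table 1 gives the range as 1 to 7. Under {18a}, dose is recorded by the provider after each session.
- **Provider.** "patients with a WHO-5 score < 50 points are offered PST provided by either the trained GP or practice staff". No rule is stated for who treats whom.
- **Controls.** "In the control protocol, patients receive the usual care".
- **Stopping.** Under {11b}, patients may withdraw at any time, and the intervention ends if severe psychopathological symptoms develop.
- **Randomisation.** Under {16a}, the unit is the general practice.

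The statistical section on process outcomes {20a} separately plans descriptive analyses of dose, among other measures, and says: "Process outcome data will be combined with effect outcome data to explore the associations between process and effect measures".

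**The concern.** A subgroup effect compares intervention with control among patients who share a characteristic. That requires the characteristic to be defined in both conditions and to be unaffected by allocation. Neither holds here: a control patient has no session count and no PST provider.

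Two analyses remain possible, and neither isolates dose or provider. One sets each dose or provider group against all controls, which compares a selected part of the intervention condition with an unselected control group. The other compares dose or provider groups within the intervention condition, which is an observational comparison because neither variable is randomised.

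At stake is the secondary message of the trial. The Discussion expects it to offer insight into moving psychological treatment from GPs to practice staff, and the provider contrast bears directly on that. A dose contrast could likewise be read as advice on how many sessions are worthwhile. Either could mislead even if PST works equally well for everyone.

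**Working it through.** **1. Is the subgroup defined in both conditions?**

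| Variable in {20b} | Known before allocation? | Defined for controls? |
|---|---|---|
| Sex, age, socioeconomic status, diagnosis, health literacy | Patient characteristic, not produced by PST | Yes |
| Practice size | Yes | Yes |
| Sessions completed | No, recorded after each session | No |
| Actual provider of PST | No, defined by who delivered it | No |

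The last two rows fail both tests.

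**2. Can dose be related to prognosis?** The article supplies one link itself: under {11b}, severe deterioration ends the intervention and so lowers the count. Voluntary withdrawal is a second route, of unknown direction. The covariates named for the primary model (age, gender, socioeconomic status) do not capture clinical course.

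**3. Size of a spurious dose slope.** The plan has no figure of its own on this point, and the article states no PHQ-9 SD, so the inputs are assumptions: no true dose effect; outcome SD 5 points; session SD 2, which is what equal use of 1 to 7 sessions gives, since √((49 − 1)/12) = 2; correlation r between prognosis and sessions.

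Spurious slope = r × SD(outcome) / SD(sessions). The difference between 1 and 7 sessions is 6 times the slope.

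| r (either sign) | Slope, points per session | 1 v 7 sessions, points |
|---|---|---|
| 0 | 0 | 0 |
| 0.1 | 0.1 × 5/2 = 0.25 | 1.5 |
| 0.2 | 0.2 × 5/2 = 0.50 | 3.0 |
| 0.3 | 0.3 × 5/2 = 0.75 | 4.5 |

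For scale, the PHQ-9 severity bands in Table 2 are about 5 points wide.

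**4. Would it show up as a finding?** This was simulated with 94 patients per condition (half of the planned 188, an assumed split), a constant treatment effect of −0.4 SD, zero dose effect, sessions spread evenly over 1 to 7, no clustering, and 4,000 runs per setting.

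| r | Mean slope, SD per session | Runs with a nominally significant slope (5%) |
|---|---|---|
| 0 | 0.00 | about 6% |
| ±0.1 | ±0.05 | about 15% |
| ±0.2 | ±0.095 | about 46% |
| ±0.3 | ±0.14 | about 80% |

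At an SD of 5, 0.14 SD is 0.70 points per session, close to the 0.75 from the formula. With 75 per condition (94 less 20% loss), the rate at ±0.3 is about 71%.

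Setting dose groups against all controls does not help. The true effect is −0.40 SD in both groups. At r = −0.3 the apparent effects are −0.14 SD (1–3 sessions) and −0.61 SD (4–7 sessions); at r = +0.3 they are −0.67 and −0.19. The ordering reverses with the sign of r, which the article does not let anyone predict.

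No figure is put on the provider contrast, because neither the split between GPs and staff nor the way patients reach them is given.

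**The case against.** The strongest reply is that the section calls these analyses exploratory, that the primary and intention-to-treat analyses are untouched, and that the estimator may be set out in an analysis plan not shown here. All three statements are correct, and they limit the consequence. They do not remove the point. The exploratory label warns of weak evidence and multiplicity; it does not make an undefined contrast interpretable. Nor is the point that detail is missing: the article positively classes two post-allocation variables as subgroups and speaks of their impact.

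A reader might infer three stronger things that the documents do not support:

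- **That the results will reflect prognosis rather than dose or provider.** This is not shown. The bias is zero if sessions are unrelated to prognosis, and the correlation is unknown.
- **That patients are steered to the GP or to staff according to need, or that early recoverers stop while the most distressed continue.** The article says neither. Provider may follow practice staffing, which the pre-study meeting maps.
- **That the mediator and process analyses share the fault.** Under {18a}, "data on mediators and unintended consequences come from questionnaires completed by both healthcare providers and patients" after the final PST session, which is ordinary process evaluation. The statistical section promises only descriptive analyses and associations for these data, and claims no mediated effect.

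The 4.5-point figure should also not be quoted alone: it pairs the largest tabulated correlation with the extreme comparison of 1 with 7 sessions. At r = 0.1 the same comparison gives 1.5 points.

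**Conclusion.** The point holds in limited form. Sessions completed and actual provider are not valid effect-modifying subgroups: they follow allocation, exist only under the intervention and are not randomised. Any contrast on them may be confounded, in either direction. Under the stated assumptions the spurious dose slope runs from zero (no correlation) through 0.25 to 0.75 PHQ-9 points per session for correlations of 0.1 to 0.3. The correlation and both SDs are assumptions, not document figures. The primary analysis is unaffected; what is at risk is a secondary conclusion on dose or on task-shifting. Practice size is a sound subgroup and is not part of the criticism.

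**What to change.** 1. In {20b}, keep as subgroup-by-condition interactions only baseline patient characteristics (with mental-health severity taken at baseline) and practice characteristics fixed before allocation, including practice size.
2. Move sessions completed and actual provider to the process analyses in {20a}. Describe them as non-causal associations within the intervention condition, adjusted for baseline PHQ-9. That adjustment reduces confounding but cannot remove the part that arises from clinical course after baseline.
3. If an effect of receiving PST is wanted, estimate a complier-average effect with exposure defined as at least one session and practice condition at enrolment as the instrument, in a mixed model that adjusts for calendar period, with its assumptions stated. A higher session threshold should not be used as the exposure: patients below it still receive PST, which breaks the exclusion restriction.
4. Analyse a planned-provider variable at practice level only if it was in fact recorded before randomisation. The article says that the pre-study meeting maps staff composition, not that it records a planned PST provider. With about 14 practices such an interaction would be imprecise.

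**Cost.** Items 1 and 2 are changes of wording and need no new data. The complier estimate is less precise than the intention-to-treat estimate, rests on the same enrolment assumptions (the condition is known to the professional who enrols the patient), and does not answer the dose-response question. The trial gives up a causal statement on dose or provider that its design does not support.

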### Methods in analysis to handle protocol non-adherence and any statistical methods to handle missing data {20c}

The intention-to-treat analysis will be supplemented with a sensitivity analysis employing multiple imputation models for handling missing values to investigate the potential impact of missing data and attrition.

### Plans to give access to the full protocol, participant-level data, and statistical code {31c}

This study protocol covers all aspects of the trial. Survey data and patient outcomes are not publicly available, but deidentified data are available upon reasonable request to the corresponding author. The statistical code will be published in the manuscripts describing the effect evaluation.

### Oversight and monitoring

#### Composition of the coordinating centre and trial steering committee {5d}

Throughout the development phase, a steering committee consisting of all authors met monthly to discuss and plan the trial. During the trial, this group will meet every 3 months to discuss the trial progress. During the enrolment period, day-to-day support and continuous monitoring of the trial for operational issues will be carried out by a group of six researchers, who will meet on a weekly basis.

#### Composition of the data monitoring committee, its role, and reporting structure {21a}

The data monitoring committee comprises the day-to-day support group (six researchers) together with the data manager, who is in charge of the Healthy Mind website database (sundtsind.au.dk). The data collection is continuously monitored throughout the trial period.

#### Adverse event reporting and harms {22}

The intervention is a well-known treatment for mental health issues and is considered safe. Thus, severe adverse effects and harms are not expected. If healthcare professionals delivering the intervention suspect that the intervention has resulted in adverse events or harms, they will contact the research group immediately.

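### Reported harms can arise only in patients who receive PST, so they cannot be compared with usual care; the symptom scales measured in both groups could support a comparison of worsening, but are described only as mean changes

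*Protocol article*

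**What the plan says.** The section on adverse event reporting and harms {22} gives one procedure: "If healthcare professionals delivering the intervention suspect that the intervention has resulted in adverse events or harms, they will contact the research group immediately". Its stated reason is that the therapy is well known and considered safe: "Thus, severe adverse effects and harms are not expected".

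Under the data collection plans {18a}, the paragraph on process outcomes adds a second source: "data on mediators and unintended consequences come from questionnaires completed by both healthcare providers and patients after the patient’s final PST session". It also plans interviews with 10 selected patients after their final session, and "The interview guide will focus on reach, fidelity, mediators, and unintended consequences". The statistical methods section treats unintended consequences descriptively.

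The section on discontinuing interventions {11b} ends PST if severe psychopathological symptoms develop, but names no recording step in either group. Blinding does not apply {17a}.

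Table 1 and the mental health outcomes paragraph of {18a} have PHQ-9, GAD-7 and WHO-5 (and PAID-5 in type 2 diabetes) completed at baseline, 6 and 12 months by all enrolled patients. The outcome and statistical sections describe these scores as mean changes.

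**The concern.** The reporting rule has two conditions: the reporter delivers PST, and the reporter suspects that PST caused the event. Neither can hold for a patient under usual care. In the intervention group, the person who judges causality is the person giving the treatment, in an unblinded trial.

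Patients are enrolled because their well-being is poor and are followed for a year, so some will deteriorate in either group. A one-sided count filtered by causality can mislead in both directions. Background deterioration may be set against PST with nothing to compare it to, or a near-zero count may be taken to confirm that PST is as safe as usual care. Mean changes do not show how many patients got worse.

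This concerns what is collected. An analysis plan can add an endpoint from existing scores, but it cannot recover events for which there was no reporting route.

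**Working it through.** The plan gives no figure for harms, so there is none to reproduce. The check has three steps.

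**1. Harm sources by group**

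| Source (section) | PST | Usual care | Needs provider suspicion |
|---|---|---|---|
| Adverse event contact {22} | yes | no | yes |
| Unintended-consequences questionnaires {18a} | yes, after final session | no | no (patients answer too) |
| Interviews, 10 patients {18a} | yes, after final session | no | no |
| Referrals and talk therapy (Discussion) | – | yes, but care use, not harms | – |
| PHQ-9, GAD-7, WHO-5 (Table 1) | yes | yes | no |

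Only the last row measures patients' state in the same way in both groups.

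**2. What the adverse event route would yield**

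Expected reports = n × event rate × P(provider suspects PST).

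Assumptions: 188 / 2 = 94 enrolled per group; true rate 10% in both. The rate and the suspicion probabilities are not in the protocol.

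- PST, suspicion 10%: 94 × 0.10 × 0.1 = 0.9
- PST, suspicion 30%: 94 × 0.10 × 0.3 = 2.8
- PST, suspicion 50%: 94 × 0.10 × 0.5 = 4.7
- Usual care: 94 × 0.10 × 0 = 0

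The true rates are equal, yet the reported counts differ by an amount set only by the suspicion probability.

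**3. What a comparison of measured worsening could deliver**

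Inputs: 188 patients and 20% loss to follow-up (Sample size {14}). Analysed: 188 × 0.8 = 150.4, or about 75 per group if split equally (assumption). Worsening is assumed to be 10% in each group.

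- 95% half-width, no clustering or period adjustment: 1.96 × √(2 × 0.1 × 0.9 / 75) = 0.096, or about ±10 points.
- Unequal split: the dates in Trial design {8} span about 14.5 months, with transitions at 4 and 8 months. With even recruitment and equal clusters, the control share is ((4 + 8) / 2) / 14.5 = 41%, giving about 62 and 88 patients. The half-width is 1.96 × √(0.09 × (1/62 + 1/88)) = 0.097, almost unchanged.
- Period adjustment matters more. Both conditions run side by side only from month 4 to month 8. If each of the three steps gets its own effect and clustering is ignored, only that step is informative: 150.4 × 4 / 14.5 = 41.5 patients, about 20.7 per condition. The half-width is 1.96 × √(2 × 0.09 / 20.7) = 0.18, or ±18 points.
- Power with 75 per group, no clustering or period adjustment: about 40% for 10% versus 20% worsening, and 68% for 10% versus 25%.

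The comparison is feasible but imprecise.

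**The case against.** Four points can be made for the plan.

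- *Harms are not captured solely through the provider's suspicion.* A reader of {22} alone might infer that they are. The process-outcome questionnaires ask patients directly, and the interviews cover the same topic. This stands, but both sources are confined to PST recipients and leave the control side empty.
- *A safety comparison is not impossible.* A reader might infer that it is. The symptom scales are collected in both groups, and the primary and secondary analyses would show a net worsening under PST. This stands as well: what cannot be compared is reported harms. Exploratory subgroup analyses, including by severity of mental health outcomes, are also planned, although they do not count patients who deteriorate.
- *A worsening threshold and its model belong in an analysis plan.* This is fair. That no such endpoint appears in the article is not itself an error, and the statement "This study protocol covers all aspects of the trial" sits under data and code access, so it does not show that no analysis plan exists. The objection does not reach the capture rule, which the article fixes.
- *Early stoppers are not shown to be missed.* A reader might infer that patients who leave PST because they feel worse are never asked. Patients may have one to seven sessions, and the final session may simply be the last one attended. The text is ambiguous here, not shown to be wrong.

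**Conclusion.** The point holds for reported harms. The adverse event procedure is limited to events that providers of PST attribute to PST, and unintended consequences are collected only after PST. The control count is zero by construction, so these data support no statement about harm relative to usual care. The 0.9 to 4.7 reports against 0 illustrate this under an assumed 10% event rate and assumed suspicion probabilities; the structural zero needs no assumption.

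The documents do not support the wider conclusion that the trial can say nothing about comparative safety, because symptom scores exist in both groups. A comparison of worsening would be weak: about ±10 percentage points at best under the stated assumptions, and nearer ±18 if each step has its own effect. It could reveal a large excess of deterioration but could not establish safety.

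**What to change.** 1. Label provider adverse event reports and unintended consequences as intervention-only in the plan and in every table, and state that no comparative safety conclusion will be drawn from them.
2. Prespecify, before the follow-up data are analysed, the proportion of patients in each group whose PHQ-9 (and GAD-7) rises from baseline by a stated threshold at 6 and 12 months. A rise of 5 points, about one severity band in Table 2, is one example; the choice is the investigators'. Use the clustering structure of the primary analysis, adjust for calendar period, and report the estimate with its interval, not only a test.
3. State that the unintended-consequences questionnaire is triggered by the last session attended, including after early stopping, and report how many PST recipients were sent it and how many answered.

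The cost is one extra analysis and table from data already collected, with the low precision shown above. Recruitment was due to end in January 2024, so any change to the questionnaire trigger may come too late for patients who had already stopped. For them, item 3 can only clarify and report what was done. Items 1 and 2 need no new data.

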#### Frequency and plans for auditing trial conduct {23}

Formal trial auditing will not be carried out.

